**Fig 1 pone.0325763.g001:**
[figure not shown]
SPIRIT schedule of enrolment, interventions and assesments.

**Fig 2 pone.0325763.g002:**
[figure not shown]
Study design of the serious game intervention.

The literature review process, the design of the psychological content of *emoTICare*, and the technological design of the *serious game* were conducted from December 2022 to June 2024. In July and August 2024, a beta study (pilot study) was carried out with a smaller sample of adolescents without Type 1 Diabetes Mellitus, during which the *emoTICare* program was tested to correct any potential errors or issues that arose during gameplay, as well as to gather feedback from the adolescents. Since September 2024, recruitment has commenced for the study sample of adolescents with Type 1 Diabetes Mellitus.

An accidental or convenience sampling method was employed. Participants were recruited as follows: all diabetes-related associations in Spain (over 100) were contacted via email and/or phone to request their voluntary participation in the study. These associations were asked to disseminate the study information to their members so that interested individuals could contact the researchers via email to participate. Regarding potential confounding variables, we acknowledge that differences between groups may arise due to the non-randomized recruitment method. To address this, we collected demographic and clinical variables (e.g., age, gender, diabetes type, disease duration) to assess and statistically control for potential confounders in the analyses.

In terms of selection bias, the recruitment process relied on voluntary participation through patient associations, which may lead to an overrepresentation of individuals who are more engaged in diabetes-related activities and support networks. This potential bias was mitigated by reaching out to a broad range of associations across Spain, ensuring geographic and organizational diversity in participant recruitment.

The phase encompassing the evaluation of the variables of interest, T1-T2-T3, will take place through the survey platform of the Universitat de València, Limesurvey, from September 2024 to the end of February of 2027. The response platform for the questionnaire battery includes a consent form for anonymous participation in the study. In this platform, informed consent will be obtained from the parents or legal guardians of the participants, as well as from the minors themselves, ensuring that all are informed about the anonymity and confidentiality of their data, confirming that their participation in the study is voluntary.

To access and play the *emoTICare serious game* online for six weeks (one week per mission of the game), participants will be provided with a link at the end of the evaluation survey conducted at T1. This *serious game* contains six distinct areas, each designed to be completed within a maximum of one week, thus allowing sufficient time to progress at different paces. During the period in which the adolescents are completing the *serious game*, an email address and a mobile phone number will be made available for participants to contact in case they need assistance (see Table 1).

**Table 1 pone.0325763.t001:** Intervention timeline.

				Timeline (in months)																															
	2024							2025												2026												2027			
	Jun	Jul	Aug	Sep	Oct	Nov	Dec	Jan	Feb	Mar	Apr	May	Jun	Jul	Aug	Sep	Oct	Nov	Dec	Jan	Feb	Mar	Apr	May	Jun	Jul	Aug	Sep	Oct	Nov	Dec	Jan	Feb	Mar	Apr
**Phase I**																																			
Enrollment and sample	★	★	★	★	★	★	★	★	★	★	★	★	★	★	★	★	★	★	★	★	★	★	★												
Assessment T1				★	★	★	★	★	★	★	★	★	★	★	★	★	★	★	★	★	★	★	★	★	★	★									
**Phase II**																																			
Control Group																																			
Experimental Group (*emoTICare* implementation)						★	★	★	★	★	★	★	★	★	★	★	★	★	★	★	★	★	★	★	★	★	★	★							
**Phase III**																																			
Assessment T2								★	★	★	★	★	★	★	★	★	★	★	★	★	★	★	★	★	★	★	★	★							
Preliminary data analysis																				★	★	★	★	★	★	★	★								
Dissemination of preliminary results																					★	★	★	★	★										
**Phase IV**																																			
Assessment T3													★	★	★	★	★	★	★	★	★	★	★	★	★	★	★	★	★	★	★	★	★		
Final data analysis and dissemination																												★	★	★	★	★	★	★	★

### Sample size

In Spain, the report on “Prevalence of Diabetes Mellitus” [50] highlights that more than three million people in the country have diabetes, of which 3.4% have Type 1 Diabetes Mellitus (T1DM). The Spanish Diabetes Society [51] estimates that T1DM accounts for 1 in every 10 cases in Spain, totaling approximately 90,000 individuals with this condition. Specifically, the incidence of diabetes in individuals under 15 years old varies between 11 and 24 cases per 100,000 inhabitants per year [51].

To determine the sample size, we used a 95% confidence level and a 5% margin of error, which is a standard approach in medical and epidemiological research. This calculation was based on the estimated population of individuals with T1DM under 15 years of age (approximately 90,000 individuals). Considering the anticipated dropout rate and the expected effect size, the total sample size was calculated to be 372 participants. This estimate assumes a normal distribution of the population and that the outcomes of interest are representative of the general T1DM population in Spain. Assumptions made during the calculation include: A 95% confidence level and 5% margin of error; A normal distribution of the studied variables, consistent with similar research in the field.; A moderate effect size based on previous studies investigating similar interventions and a 20% dropout rate, which is typical for this type of intervention study.

Limitations of the sample size calculation include potential variability in the effect size, which could differ from our assumptions. Additionally, since participants are recruited through specific diabetes associations, this sample may not fully represent the broader T1DM population, potentially introducing selection bias. Given the potential variability in healthcare access, lifestyle factors, and diabetes management across different regions, participants’ region of origin was recorded to assess potential regional differences. This information allows us to explore whether geographical factors may influence the study outcomes and, if necessary, include region as a covariate in statistical analyses to control for potential biases due to regional heterogeneity.

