## Introduction

Adolescence is a developmental stage characterised by significant physiological, social and psychological transformations [1]. This period is characterised by a combination of challenges and opportunities, as young individuals commence the process of defining their identities [2] and assuming an increasing array of responsibilities [3,4]. These transitions can be particularly challenging for adolescents [5,6], with the potential to have a significant impact on their quality of life and psychological well-being [7].

The presence of a chronic illness (CI) can further compound the challenges faced by adolescents [8,9]. According to the World Health Organization (WHO), the most prevalent chronic diseases include cardiovascular conditions, cancer, chronic respiratory diseases, and diabetes [10]. Of these, Type 1 Diabetes Mellitus (T1DM) is a particular focus, given its propensity to emerge during childhood and adolescence, although it can develop at any age [11]. T1DM is the most prevalent chronic endocrine disorder during childhood [12–15] and remains one of the most frequent chronic illnesses in adolescence [16–18]. The incidence of T1DM is highest during preadolescence and adolescence, especially between the ages of 10 and 14–15 [2,11]. In 2021, the global incidence of T1DM among children and adolescents under 15 was 651,700 cases, with 108,200 new cases reported annually. This upward trend is attributable to elevated incidence rates and reduced mortality [19].

The underlying pathophysiology of T1DM is the destruction of pancreatic β-cells, resulting in a deficiency in insulin production [11,15,20]. The management of this condition necessitates rigorous blood glucose monitoring, insulin therapy, diabetes education, medications, regular physical activity, and dietary control [21,22]. Without adequate management, T1DM can lead to complications affecting various organs and systems, increasing the risk of severe and potentially life-threatening conditions [2,23]. Furthermore, the impact on the quality of life of adolescents with T1DM is significant [17].

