Secondly, incidental sampling may hinder the generalization of the program’s results, as the sample may not fully represent the wider population of adolescents with Type 1 Diabetes. Thirdly, the online and remote format of the evaluation process, along with the use of the emoTICare program, may present challenges in ensuring proper completion, potentially increasing the likelihood of experimental mortality. Moreover, the online format could impact participant engagement, as the lack of direct interaction may lead to decreased attention or motivation. This is particularly relevant as maintaining participant motivation throughout the study period is a challenge in long-term interventions, and participants may experience fatigue or loss of interest over time. Additionally, biases in self-reported data could arise, as participants might provide socially desirable answers or misinterpret the questions, affecting the accuracy of the data. Conversely, per-protocol analysis (PP) provides a clear understanding of the potential benefits of treatment by focusing on subjects who have completed their assigned treatment regimen. However, it is limited in that it does not account for real-world challenges to adherence in real-world settings.

A further limitation of this study is the absence of specific data on the incidence of type 1 diabetes in individuals under 16 years of age. Instead, the incidence in individuals under 15 was used as a reference. It is acknowledged that this may result in under- or overestimation, owing to the exclusion of data from 15–16-year-olds. It is also noted that, given the relatively narrow additional age span (one year), any deviation in incidence is unlikely to significantly affect the overall power or feasibility estimates of the study. Incidence figures for individuals under 15 years are extensively utilised in international diabetes surveillance and are regarded as robust and comparable across populations. Given that the majority of the target population falls within the 12–14 age range, it was considered reasonable to use incidence data for individuals under 15 years as a proxy for estimating the expected number of eligible participants. Furthermore, the incidence of type 1 diabetes between ages 15 and 16 does not markedly deviate from that observed in the immediately preceding years, particularly in populations with relatively stable incidence curves.

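### The sample size of 372 rests on a survey margin-of-error rule that does not size a two-arm comparison, and 372 does not follow from the inputs stated for it

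*Protocol article*

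**What the plan says.** The Sample size section of the protocol article opens with the burden of diabetes in Spain. It attributes to the national diabetes society the estimate that "T1DM accounts for 1 in every 10 cases in Spain, totaling approximately 90,000 individuals with this condition", with no age limit. It then sets out the calculation: "we used a 95% confidence level and a 5% margin of error", and "This calculation was based on the estimated population of individuals with T1DM under 15 years of age (approximately 90,000 individuals". The result follows: "Considering the anticipated dropout rate and the expected effect size, the total sample size was calculated to be 372 participants". The listed assumptions are the confidence level and margin, normality, an effect described only as moderate, and 20% dropout. No numerical effect size, standard deviation, outcome, test or power appears.

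The trial being sized is a randomised two-arm comparison with equal allocation probability (Study design). The between-group change is to be analysed by MANCOVA and ANCOVA with the pre-intervention score as covariate (Data analysis). The limitations in the Discussion return to the population figure and say that "any deviation in incidence is unlikely to significantly affect the overall power or feasibility estimates of the study".

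**The concern.** Confidence level, margin of error and population size are the inputs for estimating one proportion in one sample. That formula has no term for a difference between arms, for power or for an effect size, so it cannot show that the trial can answer its question. Naming an effect size among the assumptions does not repair this, because nothing in the stated method uses it.

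Two further problems sit inside the derivation. The same 90,000 carries two incompatible labels within two paragraphs, and neither matches the enrolled ages of 12 to 16. The dropout allowance, said to have been considered, is not visible in the result.

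At stake is the only sample-size rationale in the article. As written, it does not tell a reader what difference the trial was planned to detect.

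**Working it through.** **Inputs from the article.** Total 372; confidence 95%; margin 0.05; population 90,000; dropout 20%; allocation 1:1 in expectation; significance at .05; six primary outcomes (Measurements). **Assumed because not given:** p = 0.5 in the survey formula, two-sided testing, and d = 0.3 to 0.5 for the effect.

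**1. The plan's own route.**
- n0 = z² p(1 − p)/e² = 1.96² × 0.25/0.05² = 384.16, so 385 for an unlimited population.
- Finite-population correction: n = n0/(1 + (n0 − 1)/N) = 384.16/(1 + 383.16/90,000) = 382.5, so 383.
- With 20% dropout: 383/0.8 = 478.75, so 479. Multiplying instead: 383 × 1.2 = 459.6, so 460.
- Stated: 372. Before dropout the gap is 11 (383 against 372, about 3%). After dropout it is 107 (or 88).
- Solving the same formula for 372: N = (n0 − 1)/(n0/372 − 1) ≈ 11,700, with no dropout. Within the survey formula, an exact 372 therefore contradicts two stated inputs.
- Read the other way, 372 × 0.8 ≈ 298 remain, and the margin is 0.05 × √(384.16/298) = 5.7%, not 5%.

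**2. The 90,000.**
- First use: "totaling approximately 90,000 individuals with this condition", for all ages. This fits the section's other figure: 3.4% of three million is 102,000.
- Second use: those under 15. The Introduction reports that "the global incidence of T1DM among children and adolescents under 15 was 651,700 cases", so 90,000 would be 90,000/651,700 = 13.8% of the world total.
- The section also says that "the incidence of diabetes in individuals under 15 years old varies between 11 and 24 cases per 100,000 inhabitants per year". At the upper rate, with constant incidence and a mean of 7.5 years at risk (assumed), 90,000 existing cases would need 90,000/(0.00024 × 7.5) = 50 million children under 15.
- Effect on the result: the correction at 90,000 takes 385 to 383, about 2 participants.

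**3. Two-arm comparison.** Two-sample t-test, two-sided .05, d = 0.5 assumed:

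| Power | Per arm | Analysed | With 20% dropout |
|---|---|---|---|
| 80% | 64 | 128 | 160 |
| 90% | 86 | 172 | 215 |

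By the normal approximation, other unstated inputs come close to 372: d = 0.5 at 99% power gives 368 and d = 0.325 at 80% gives 374, both with dropout. So 372 is neither confirmed nor excluded by this route; it cannot be checked.

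**4. What 372 delivers.** 372 × 0.8 ≈ 298, or 149 per arm:

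| d (assumed) | Power at .05 | Power at .05/6 |
|---|---|---|
| 0.5 | 99% | 95% |
| 0.4 | 93% | 79% |
| 0.3 | 73% | 47% |

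Detectable d, unadjusted: 0.33 (80% power) or 0.38 (90%) at .05, and 0.41 (80%) at .05/6. ANCOVA multiplies these by √(1 − r²), where r is the T1–T2 correlation. For r = 0.5 to 0.6 (assumed), the 0.326 at 80% power becomes 0.28 to 0.26.

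**The case against.** The strongest reply is that the number is adequate whatever its origin. If moderate means d = 0.5, the trial has 99% power for one outcome and 95% with a Bonferroni split over six. That stands, and it limits the point to the justification. It depends on an assumed reading of moderate, though, and power is 73% at d = 0.3, or 47% at .05/6.

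A second reply is that 383 is within about 3% of 372. That is true before dropout, so the failure to reproduce rests mainly on the dropout step. But the text says dropout was considered, and even an exact match would leave the wrong method standing.

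Third, the Discussion sentence mentions feasibility as well as power, and its paragraph is mainly about the number of eligible adolescents. That is fair: as a recruitment remark it is harmless. Only the reference to power is misplaced, since incidence does not enter the power of this comparison.

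A reader might infer three stronger things that the article does not support: that the trial is underpowered, that the 90,000 error drives the sample size, or that a null result could not be interpreted. The first is not shown for a moderate effect read as d = 0.5. The second concerns about 2 participants. On the third, the estimate and its confidence interval can be read whatever the planning text says.

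**Conclusion.** The point holds as an invalid justification. The method is wrong for the design, the population figure contradicts itself, and 372 does not follow from the stated inputs (383 before dropout, 479 or 460 after it). The reproduction rests on p = 0.5, the usual choice but not stated. Agreement with the moderate effect cannot be judged without an effect size, test and power.

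The detectable-effect figures rest on 298 analysed. That is an upper figure if the 20% does not cover the other exclusions: incomplete treatment or non-adherence (Data analysis), failure to complete all three time points (Measurements), and invalidation by the infrequency scale (Psychological variables). The article does not say whether it does.

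The text should be corrected before results are reported, because this is the trial's only stated size rationale and the correction is cheap.

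**What to change.** Change the text and leave enrolment as it is.

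- Delete the margin-of-error and population derivation from Sample size.
- Correct the 90,000 so that it carries one label, all people in Spain with type 1 diabetes.
- In the Discussion, remove the link between incidence and power; the remark on feasibility can stay.
- State 372 as a fixed, feasibility-based size, if the sponsor confirms that this is how it was reached. Report what it can detect and label this as a detectable effect for a fixed number, not as the original planning basis; recruitment began in September 2024.
- Suggested content: 372 randomised, 20% loss, about 298 analysed, detectable d = 0.33 at 80% power (two-sided .05) or 0.41 at .05/6. Say that both are unadjusted and so conservative for the planned ANCOVA, about 0.28 to 0.26 at .05 if the T1–T2 correlation is 0.5 to 0.6 (assumed).
- Say whether the 20% covers the per-protocol, three-time-point and infrequency-scale exclusions. If not, describe 298 as an upper figure.

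The cost is a few sentences and a rationale that reads slightly less favourably. The article says that recruitment and data collection were not complete, so the correction can precede the results.

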### Eligibility and recruitment criteria

To be included in this study, participants must be aged between 12 and 16 years, have a diagnosis of Type 1 Diabetes Mellitus (T1DM) for at least six months, not have a diagnosis of any other chronic physical illness, and not have any prior diagnosis of psychological disorder. Additionally, they must have completed the informed consent form prior to participation.

Exclusion Criteria: Physical diagnosis other than type 1 diabetes mellitus; No access to internet or new technologies; Not speaking Spanish.

The opportunity to participate in the study, along with relevant information will be communicated through various channels. In order to recruit participants, the study will be publicized throughout Spain through the dissemination channels of diabetes associations. To participate, parents or legal guardians of the adolescents must provide prior written informed consent.

Regarding the status and timeline of the study (we offer an estimate): A) participant recruitment will be completed by April of 2026; B) data collection will be completed by February of 2027 and C) final results are expected by April of 2027. None of these stages have already been completed.

### Interventions

The *emoTICare* technological platform intervenes with participants through a *serious game*, which is defined as a video game primarily designed to teach or provide the player with certain skills that serve to achieve a purpose beyond the game itself [43,44]. Accordingly, using the theoretical model of chronic illness adjustment developed, a series of playable areas were created that address the main factors promoting adaptive adjustment to chronic illness, specifically Type 1 Diabetes Mellitus in the adolescent population.

Firstly, when selecting the narrative context of the game, the aim was to generate a certain degree of immersion, as this has been shown to increase the likelihood of changing beliefs and attitudes in the real world [52].

### Development of the platform

Health-related quality of life (HrQoL) is a multidimensional construct that encompasses the physical, emotional, and social aspects of well-being. Unlike general quality of life, HrQoL primarily refers to the effect that illness and its subsequent treatment have on the various functional areas of an individual [53–55]. As previously explained, adolescence is a stage of life marked by critical changes that require personal skills to manage. Given the importance of coping with a chronic illness such as Type 1 Diabetes Mellitus (T1DM) during this period, and the need to promote socioemotional resources during this developmental transition to enhance adolescents’ quality of life, an initial review of the existing scientific literature on conceptual models of illness adjustment and health prevention was conducted. This review sought to identify common indicators of optimal positive development during adolescence, establishing a framework to promote adolescent quality of life.

As a result, a model was developed—the *Disease Adjustment Model from an Integrative Perspective* (DAMIP) [56]—which integrates a solid theoretical framework to facilitate the design, justification, and development of psychological interventions aimed at preventing psychological difficulties and enhancing adjustment to chronic illness during adolescence, thus improving quality of life and emotional well-being in this population.

The theoretical model was developed through the integration of different concepts and indicators present in pre-existing theoretical models, leveraging their complementarity. DAMIP draws upon Livneh’s Integrative Model [57,58], supplemented by Antonovsky’s Salutogenic Model [59], Leventhal’s Self-Regulation Model of Illness [60], and Hochbaum’s Health Belief Model [61], as well as elements from the proposal for promoting quality of life in adolescents from the National Academies of Sciences, Engineering, and Medicine (Health and Medicine Division; Division of Behavioral and Social Sciences and Education; Board on Children, Youth, and Families; Committee on Applying Lessons of Optimal Adolescent Health to Improve Behavioral Outcomes for Youth), led by Kahn and Graham [62], and the Kidscreen Project by Ravens-Sieberer et al. [63,64]. The DAMIP model provides the scientific community with a theoretical framework for optimizing socioemotional diagnosis and intervention in this population.

Based on the theoretical configuration of the DAMIP model, its core elements were incorporated into the development of the *emoTICare serious game*. The game consists of six missions aimed at fostering the most frequently cited concepts related to the structure underlying optimal development and well-being, which are crucial when implementing interventions to improve the biopsychosocial health of adolescents.

